## Abstract

**Background:**

The CORONIS Trial was a 2×2×2×2×2 non-regular, fractional, factorial trial of five pairs of alternative caesarean section surgical techniques on a range of short-term outcomes, the primary outcome being a composite of maternal death or infectious morbidity. The consequences of different surgical techniques on longer term outcomes have not been well assessed in previous studies. Such outcomes include those related to subsequent pregnancy: mode of delivery; abnormal placentation (e.g. accreta); postpartum hysterectomy, as well as longer term pelvic problems: pain, urinary problems, infertility. The Coronis Follow-up Study aims to measure and compare the incidence of these outcomes between the randomised groups at around three years after women participated in the CORONIS Trial.

**Methods/Design:**

This study will assess the following null hypotheses: In women who underwent delivery by caesarean section, no differences will be detected with respect to a range of long-term outcomes when comparing the following five pairs of alternative surgical techniques evaluated in the CORONIS Trial:

1. Blunt versus sharp abdominal entry

2. Exteriorisation of the uterus for repair versus intra-abdominal repair

3. Single versus double layer closure of the uterus

4. Closure versus non-closure of the peritoneum (pelvic and parietal)

5. Chromic catgut versus Polyglactin-910 for uterine repair

The outcomes will include (1) women’s health: pelvic pain; dysmenorrhoea; deep dyspareunia; urinary symptoms; laparoscopy; hysterectomy; tubal/ovarian surgery; abdominal hernias; bowel obstruction; infertility; death. (2) Outcomes of subsequent pregnancies: inter-pregnancy interval; pregnancy outcome; gestation at delivery; mode of delivery; pregnancy complications; surgery during or following delivery.

**Discussion:**

The results of this follow-up study will have importance for all pregnant women and for health professionals who provide care for pregnant women. Although the results will have been collected in seven countries with limited health care resources (Argentina, Chile, Ghana, India, Kenya, Pakistan, Sudan) any differences in outcomes associated with different surgical techniques are likely to be generalisable throughout the world.

**Trial registration:**

ISRCTN31089967

## Background

Caesarean section is one of the most commonly performed operations worldwide and accounts for up to 60% of deliveries in some countries, with a rate of approximately 24.6% in the UK in 2008/2009 [1]. The operation is not performed in a standardised way, and there are variations in the surgical techniques used [2]. Caesarean section carries a risk of short-term post-operative morbidity, for example, fever, pain and postpartum haemorrhage. Also of major importance are the long-term clinical and obstetric problems such as chronic pain, infertility, bowel obstruction, abnormal placentation and its consequences, and uterine rupture. The effects of caesarean techniques on these long-term outcomes have not been well assessed in randomised controlled trials to date [3].

The MRC funded CORONIS Trial is a 2×2×2×2×2 fractional, factorial trial of different surgical techniques at caesarean section. The trial is comparing (1) blunt versus sharp abdominal entry; (2) exteriorisation of the uterus for repair versus intra-abdominal repair; (3) single versus double layer closure of the uterus; (4) closure versus non-closure of the peritoneum (pelvic and parietal); (5) chromic catgut versus Polyglactin-910 for uterine repair, on a range of short-term outcomes, the primary outcome being a composite of maternal death or maternal infectious morbidity.

### Summary of existing evidence

Existing systematic reviews of randomised controlled trials have been unable to draw clear conclusions about whether any of the techniques being compared in the CORONIS Trial are to be preferred [4-9]. Optimisation of surgical techniques may be able to reduce both the short-term and the long-term morbidity associated with caesarean section and although differences may be relatively modest, the commonness of the operation means that even small improvements in outcome may result in substantial improvements in health for many thousands of women and considerable cost savings for health services.

Short-term outcomes are the primary outcomes evaluated in most of the trials assessing alternative techniques for caesarean section. These are often surrogate outcomes and are usually only measured up to 6 weeks after the caesarean section. The most common outcomes assessed are:

• operative time and length of postoperative stay

• use of extra haemostatic sutures

• defects in the uterine scar or thickness of the uterine scar

• infection or complications of the wound

• postpartum endometritis

• decrease in postoperative haematocrit

• use of blood transfusion

• fever or postoperative febrile morbidity

• pain

Other more robust neonatal outcomes are rarely collected such as:

• neonatal death

• birth trauma

• admission to neonatal unit

It is clear that the most important differences in terms of maternal outcomes between different surgical techniques may be apparent in the long-term, including the functional integrity of the uterine and abdominal scar during subsequent pregnancies and other long-term post-operative effects such as chronic pelvic pain, infertility, peritoneal and bowel adhesions and obstruction [10]. Even in the absence of short-term effects, there may well be important long-term differences between the randomised groups (a situation not dissimilar to that seen in the MRC funded ORACLE Trial where there were no short-term differences seen [11]. However, in the 7-year follow-up of the children born to women presenting in preterm labour with intact membranes, there was an excess of cerebral palsy in the children of mothers treated with antibiotics compared with those who received placebo [12]). In CORONIS, there is a real possibility that long-term effects may go in the opposite direction to the short-term effects. For example, non-closure of the peritoneum is quicker than closure and may therefore result in less infectious morbidity in the short-term. However, it may also be associated with involuntary infertility because of excessive intraperitoneal adhesion formation.

Therefore long-term outcomes, even if uncommon, are more likely to have a higher impact on morbidity and can occasionally result in life-threatening events or even death. The long-term outcomes assessed in the few existing studies are: fertility (infertility) after caesarean section, chronic pain, dyspareunia, constipation, adhesion formation and uterine rupture [10,13-16]. Some of these outcomes can only be assessed by measuring morbidity in subsequent pregnancies or at subsequent episodes of abdominal surgery. Therefore, trials with large sample sizes are needed to ensure adequate power to draw conclusions about long-term outcomes between compared groups.

A systematic review of the literature has shown that to date there have been only three long-term follow-up studies of the existing randomised trials of caesarean section techniques. One investigated the long-term effects of single versus double layer uterine closure and two studies assessed long- term outcomes of trials comparing closure versus non-closure of the peritoneum in a subsequent pregnancy [10,13,14]. The sample sizes of these follow-up studies are small and included only 18% of the women randomised into the original trials for two of them [10,13] and 51% for the third [14]. In the only study that compared single versus double layer uterine closure, no statistically significant difference was found on the following outcomes: inter-pregnancy interval, vaginal delivery, length of hospital stay, preterm delivery, amnionitis, postpartum endometritis, placental abruption, postpartum haemorrhage, blood transfusion or uterine dehiscence. However, this was only based on a sample size of 145 women out of the 906 randomised in the original trial [13]. From the two follow-up studies of randomised trials comparing closure versus non-closure of the peritoneum (209 women in total), no differences were observed in terms of intra-abdominal adhesions (65 women evaluated out of the 360 originally randomised) [10], abdominal pain, dyspareunia, constipation, urinary symptoms and infertility (144 women included out of the 280 originally randomised) [14].

Given the relatively low incidence of uterine rupture (0.4 to 0.6% for women undergoing a trial of labour versus 0.2% for those having elective repeat caesarean) and dehiscence (1.1%) [17], attempts to detect differences in these outcomes between different surgical techniques with adequate power is challenging. However, the one large observational study that has looked at this outcome is weakened by several potentially interrelated factors [15]. For example, the caesarean technique used changed from mainly double layer closure to mainly single layer closure during the period studied, and the selection criteria for trial of labour may have changed in this time too. Thus women who had single layer closure may have been more likely to have a trial of labour. Well conducted follow-up studies of randomised trials remain the best option to evaluate these outcomes reliably.

There are still very important outcomes that have not been assessed by any randomised trial or observational study, which have major implications for the health of women and their babies. These include for example: mode of delivery of subsequent pregnancy, the risk of placenta accreta and other abnormal placentation, and postpartum hysterectomy.

Placenta accreta is strongly linked to placenta praevia, a condition recognised to increase as the number of previous caesarean sections rises [18-20]. The presence of placenta accreta is associated with major pregnancy complications, including life-threatening maternal haemorrhage, uterine rupture, peripartum hysterectomy [21] and maternal death, as well as complications associated with surgical removal including damage to bladder, ureters and other organs [22]. We know of no randomised trials comparing different techniques for caesarean section assessing this important outcome.

There has been one large observational study of peripartum hysterectomy relating this to previous caesarean section. This study [21], carried out in the UK, collected all cases of peripartum hysterectomy during a 13 month period. There were 318 confirmed cases of peripartum hysterectomy in an estimated 779,955 total births, giving an incidence of 4.1 per 10,000 total births (95% CI 3.6 to 4.5). Three hysterectomies were undertaken electively for management of malignancy with the remaining 315 undertaken for management of haemorrhage. The most commonly reported causes of haemorrhage were uterine atony (53%), morbidly adherent placenta (39%), uterine rupture (8%) and extension of uterine incision at delivery (6%). Compared with controls, women who had had a peripartum hysterectomy had over three times the odds (odds ratio 3.52, 95% CI 2.35 to 5.26) of having a previous caesarean section. This odds ratio increased with the number of previous sections such that women with a peripartum hysterectomy had over eighteen times the odds of having two or more previous sections compared to control women. In this study, two women died, a case fatality of 0.6% (95% CI 0 to 1.5%).

This study did not collect data about the surgical techniques used at previous caesarean section but it does illustrate the evidence that is beginning to emerge about the important longer term morbidity associated with caesarean section.

There are no on-going studies of long-term follow-up of randomised controlled trials of caesarean section that any of the investigators are aware of. The UK CAESAR Trial [23], which was a 2×2×2 factorial trial of (i) single versus double layer uterine closure, (ii) closure versus non-closure of the pelvic peritoneum and (iii) liberal versus restricted use of a sub-sheath drain has finished recruiting and long-term follow-up of this cohort is planned. This trial was also conducted by the National Perinatal Epidemiology Unit (NPEU) and follow-up is planned for 8–11 years after trial recruitment because the inter-pregnancy interval is substantially longer in a UK population than in the settings participating in CORONIS. A prospective meta-analysis of the trial follow-up studies (for single versus double layer uterine closure) is planned.

### The CORONIS Trial (https://www.npeu.ox.ac.uk/coronis)

The objectives of the CORONIS Trial are to determine whether there are any differences in short-term maternal morbidity when comparing five pairs of alternative surgical techniques undertaken during the time of caesarean section. Information was collected at trial entry, immediately following the operation, at discharge from hospital and at six weeks after delivery. The CORONIS Trial protocol has been published and can be downloaded free at http://www.biomedcentral.com/1471-2393/7/24.

### Trial eligibility

Women are eligible for trial entry if they are undergoing delivery by lower segment caesarean section through a transverse abdominal incision, irrespective of fever in labour, gestational age or whether they have a multiple pregnancy.

Women are not eligible if: (i) there is a clear indication for a particular surgical technique or material to be used that prevents any of the allocated interventions being used; (ii) they have had more than one previous caesarean section; (iii) they have already been recruited into the trial during a previous pregnancy.

### Trial primary outcome

Death or maternal infectious morbidity (one or more of the following: antibiotic use for maternal febrile morbidity during postnatal hospital stay, antibiotic use for endometritis, wound infection or peritonitis) or further operative procedures; or blood transfusion (>1 unit of whole blood or packed cells).

### Trial interventions

There are five pairs of interventions being tested in the trial; however, each participating hospital only takes part in three of these five possible comparisons. The non-allocated comparisons and all other aspects of the caesarean section are performed at the discretion of the surgeon.

1. Blunt versus sharp abdominal entry

2. Exteriorisation of the uterus for repair versus intra-abdominal repair

3. Single versus double layer closure of the uterus

4. Closure versus non-closure of the peritoneum (pelvic and parietal)

5. Chromic catgut versus Polyglactin-910 for uterine repair

### Factorial trials

Factorial trials maximise the efficiency of a trial by including more than one trial question into a single trial population. Instead of having one trial which compares, for example, single versus double layer closure of the uterine incision and another trial comparing closure versus non-closure of the peritoneum, both comparisons can be combined into one trial using only the number of women necessary to answer one of these questions in isolation. In the CORONIS Trial, five comparisons have been carried out in one trial. Such a design has rarely been used, but is appropriate for the evaluation of several procedures which will be used together in clinical practice. In such a trial of different caesarean section techniques, using five pairs of possible allocated interventions (1 versus “not 1”, 2 versus “not 2”, 3 vs. versus “not 3”, 4 versus “not 4”, 5 versus “not 5”), participants can receive one of 32 possible alternatives.

In the analysis of a factorial trial the same process is used for a 2×2×2×2×2 factorial design as for a 2×2 factorial design. All those allocated 1 are compared with all those allocated “not 1” regardless of what other interventions were allocated, provided that there is no interaction.

### Fractional factorial trials

In a standard 2×2×2×2×2 factorial design, all participants would receive one of 32 possible alternatives, and each of these alternatives would include five interventions. The CORONIS Trial is a fractional factorial design, and, therefore, each participant was allocated only three out of the five possible interventions. Such an incomplete factorial design was considered appropriate because it allows five surgical techniques to be tested in the same trial, but restricts the number of techniques being tested per centre and per surgeon to three. Hence, each centre was required to implement training for three (not five) surgical techniques and each surgeon was required to remember the three (not five) allocated techniques for every randomised woman.

There were two main implications of this incomplete factorial design. First, in the trial design, we ensured that a similar number of women were included in each of the five comparisons. Second, in the analysis, we will not be able to test for interactions between more than three interventions.

CORONIS recruited in excess of 15,000 women in Argentina, Chile, Ghana, India, Kenya, Pakistan and Sudan. This represents a unique cohort of women to follow up to assess and compare their long-term health outcomes between the different randomised components. In order to ensure a high rate of follow-up while maximising the number of women who will have had a subsequent pregnancy, we have chosen to follow up this cohort at least three years after their participation in CORONIS. Any longer and we risk losing women to follow-up, any shorter and we decrease the number of women who will have had a subsequent pregnancy and therefore limit our power to address important potential differences in outcome.

## Methods/Design

### The CORONIS Follow-up study

#### Objective

The objective of the CORONIS Follow-up Study is to measure and compare the incidence of outcomes at around three years between the randomised groups of women who participated in the CORONIS Trial.

#### Hypothesis

This study will assess the following null hypotheses: In women who underwent delivery by caesarean section, no differences will be detected with respect to a range of long-term outcomes when comparing the following five pairs of alternative surgical techniques:

1. Blunt versus sharp abdominal entry

2. Exteriorisation of the uterus for repair versus intra-abdominal repair

3. Single versus double layer closure of the uterus

4. Closure versus non-closure of the peritoneum (pelvic and parietal)

5. Chromic catgut versus Polyglactin-910 for uterine repair

#### Tracing women

All women participating in the CORONIS Trial have been informed that we hope to be able to interview them at least three years after they were included in CORONIS to ask them about their long-term health.

The trial entry information leaflet contains the following paragraph:

“*We are also keen to find out whether the different methods used make any difference to your long*-*term health. We would like to contact you again after the study has finished. We will ask you how you are and whether you have had any more babies*.”

In addition, at the ‘six week’ follow-up appointment, women are provided with the following letter:

“*Thank you for taking part in CORONIS and for letting us know about your health since your caesarean section*.”

*We hope to see all women who take part in the study once more. This will be three years after the caesarean section. At this visit we will also ask about your health since your caesarean section. Because a lot can happen in three years*, *we will keep in touch with you every 6 months or so to make sure we have your correct phone number and address*.

*If you have any more pregnancies or have any surgery it would be very helpful if you*, *or your doctor*, *could write these down on the CORONIS Medical Card. This will make it easier for you to remember everything that has happened since your caesarean section*.

*If you move house or change your phone number*, *please fill in the Change of Address card and send it back to the Study Office*, *or phone us. The phone number and address are*: [*details*]

“*If you do not want to take part in the study any more*, *you can let us know by phoning or writing to the Study Office. Thank you for your help with this study*.”

To facilitate long-term follow-up women have been provided with a medical card and a document bag for storing their medical information. This bag has the CORONIS Trial logo printed on the outside and contains information about letting the local Regional Trial Office know if the woman moves house or changes other contact details.

The process of maintaining contact with women who participated in CORONIS between their six week follow-up and the three year follow-up is coordinated by each Regional Trial Office to reflect differences in the circumstances between the very different settings for this trial.

#### Outcomes

The list below represents the full range of outcomes relevant to the five intervention pairs being evaluated.

#### Women’s health and mortality

1. Following the CORONIS birth and before any subsequent pregnancy, any new onset or worsening of:

i. pelvic pain

ii. dysmenorrhoea

iii. deep dyspareunia

iv. urinary symptoms of poor stream and/or frequency which did not respond to antibiotics

2. Diagnostic laparoscopy or diagnostic laparotomy (not related to pregnancy)

3. Hysterectomy or tubal/ovarian surgery (not related to pregnancy)

4. Bladder or bowel damage in those women who have had surgery, excluding diagnostic laparoscopy and diagnostic laparotomy (not related to pregnancy).

5. Following the CORONIS birth, any new onset of:

i. abdominal hernia

ii. bowel obstruction

6. Woman’s death

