** *Women’s health and mortality* **						
1 i)	Pelvic pain	s	s	s	**M**	s
ii)	Dysmenorrhoea	s	s	s	s	s
iii)	Deep dyspareunia	s	s	s	**M**	s
iv)	Urinary symptoms	s	s	s	s	s
2	Diagnostic laparoscopy or diagnostic laparotomy - not related to pregnancy	s	s	s	**M**	s
3	Hysterectomy or tubal/ovarian surgery - not related to pregnancy	s	s	s	**M**	s
4	Bladder or bowel damage – not related to pregnancy	s	s	s	**M**	s
5 i)	Abdominal hernias	**M**			s	
ii)	Bowel obstruction	s	s	s	**M**	s
6	Woman’s death		s	**M**	s	**M**

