### Analysis populations

For the primary analyses, all maternal and child outcomes will be analysed in the groups into which they were randomly allocated e.g. comparing the outcome of all women allocated “blunt abdominal entry” with all those allocated “sharp abdominal entry”, regardless of technique received. Maternal and child outcomes will be analysed for all eligible women correctly recruited for whom data are available.

The outcomes of interest for women who have a subsequent viable pregnancy, such as uterine rupture, will be analysed using two different denominators i.e. women who subsequently have at least one pregnancy and all women randomised. This will take account of the potential for differences in the pregnancy rate between the two arms being compared.

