### Primary comparative analyses

The primary analyses will be performed on each of the five pairs of surgical techniques. Outcomes will be summarised by intervention group using appropriate summary statistics (counts and percentages, means and standard deviations, or medians and inter-quartile ranges). Comparisons will be made using relative risks (RR) for dichotomous/categorical outcomes, mean differences for normally distributed continuous outcomes, or median differences for skewed continuous variables (unless the data can be transformed to normality). Analysis of time to event outcomes will employ survival analysis techniques [26].

Multiplicity of statistical testing will be addressed in the detailed statistical analysis plan.

With regard to the analysis of child outcomes, multiple births will be treated as independent events in the primary analysis, in order that relative risks may be presented.

Adjusted analyses will be performed on all comparisons to investigate the impact of minimsation factors ‘In-labour or not in-labour caesarean section’ and ‘number of previous caesarean sections (none or one)’. These will be agreed by the investigators and the Study Steering Committee and pre-specified in the SAP.

Subgroup analyses will be similarly agreed and pre-specified in the statistical analysis plan and results will be presented on forest plots, by intervention pair, wherever appropriate.

The robustness of the results will be examined in sensitivity analyses by using multiple imputation techniques to impute missing 3 year follow-up data, and also restricting analyses to a pre-specified follow-up window. Sensitivity of the effect estimates to adjustments for potential clustering of multiple births will also be examined.

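### Bladder or bowel damage (outcome 4) is worded as measured only in women operated on after randomisation, and the plan's all-women denominator is not extended to it, so a difference in harm per woman can be masked

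*Protocol article*

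**What the plan says.** All references are to the protocol article.

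- **Outcome definition** (Women's health and mortality, item 4): "Bladder or bowel damage in those women who have had surgery, excluding diagnostic laparoscopy and diagnostic laparotomy (not related to pregnancy". Items 2, 3, 5 and 6 of the same list carry no restriction to operated women.
- **Status** (Table 1): the row is labelled "Bladder or bowel damage – not related to pregnancy". It is marked M for closure versus non-closure and s for the other four pairs. Only M comparisons go in the main paper.
- **Later surgery as an outcome** (Table 1): "Hysterectomy or tubal/ovarian surgery - not related to pregnancy" is also M for closure versus non-closure, and so is bowel obstruction.
- **Mechanism** (Summary of existing evidence): of non-closure, the text says that "it may also be associated with involuntary infertility because of excessive intraperitoneal adhesion formation".
- **Denominator rule** (Analysis populations): "The outcomes of interest for women who have a subsequent viable pregnancy, such as uterine rupture, will be analysed using two different denominators". These are women with at least one later pregnancy, and all women randomised. The reason given is "This will take account of the potential for differences in the pregnancy rate between the two arms being compared".
- **General population rule** (Analysis populations): "Maternal and child outcomes will be analysed for all eligible women correctly recruited for whom data are available".
- **Effect measure** (Primary comparative analyses): "Comparisons will be made using relative risks (RR) for dichotomous/categorical outcomes".

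**The concern.** Women who are operated on after the trial caesarean form a group created after randomisation. If closure changes who comes to surgery, the operated women in the two arms are no longer comparable. If it changes how many do, any extra operations enter the denominator together with any injuries they bring. The RR among operated women then describes risk per operated woman, and a surgeon choosing between closure and non-closure cannot read from it the harm per woman.

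The authors saw this problem for pregnancy outcomes and gave a remedy with its reason. Outcome 4 has the same structure but is by definition unrelated to pregnancy, so the remedy as written does not reach it. Because outcome 4 is a main comparison for closure, the conditional RR would be the figure in the main paper.

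**Working it through.** **Inputs from the protocol.** Sample size and power gives 9,296 women per intervention pair and at least 80% response: 9,296 × 0.80 = 7,437, which agrees with the stated figure of about 7,400. With equal arms that is about 3,700 women per arm. Table 2 has no row for outcome 4, and the protocol gives neither a surgery rate nor a damage rate, so there is no stated figure for this outcome to reproduce.

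**Assumed inputs.** Surgery in 1.0% of women after closure and 1.5% after non-closure; damage in 6% of operated women in both arms.

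**Identity.** All RRs are non-closure versus closure.

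RR per woman = RR of having surgery × RR of damage among operated women

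**Numbers.**

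| | Closure | Non-closure | RR |
|---|---|---|---|
| Women followed | 3,700 | 3,700 | |
| Operated | 3,700 × 0.010 = 37 | 3,700 × 0.015 = 55.5 | 1.50 |
| With damage | 37 × 0.06 = 2.22 | 55.5 × 0.06 = 3.33 | |
| Damage among operated women | 2.22/37 = 6% | 3.33/55.5 = 6% | 1.00 |
| Damage per woman followed | 2.22/3,700 | 3.33/3,700 | 1.50 |

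The comparison among operated women shows no effect, although non-closure carries half as many injuries again per woman.

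**Range.** Take surgery in 2% to 5% of the closure arm, damage in 4% of operated women in both arms, and surgery raised 1.25-fold to 2-fold by non-closure. The RR among operated women stays at 1.00, while the RR per woman runs from 1.25 to 2.00. At the top of the range (5% v 10% surgery) the counts are 7.4/185 v 14.8/370 operated women (RR 1.00) and 7.4/3,700 v 14.8/3,700 women (RR 2.00).

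**Precision.** On the first set of figures, the standard error of the log RR per woman is about √(1/2.22 + 1/3.33) = 0.87. The approximate 95% interval around 1.50 is 0.27 to 8.2. Even at 5% v 10% surgery, power with the all-women denominator is only about 35% (two-sided 5%, normal approximation).

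**The case against.** **The wording may not set a denominator.** Surgical injury can occur only in women who have surgery, so the phrase may simply say which injuries count. The Table 1 label omits it, and the general population rule covers all eligible women with data. This reading is possible. But the general rule says who is in the analysis and does not clearly lift a restriction written into an outcome; nor did the authors rely on it for pregnancy outcomes, where they added a separate rule. The text is at best ambiguous for a main comparison, and the same sentence would settle it.

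**A difference in surgery is not predicted.** This stands. The M mark denotes interest, the stated hypotheses are null, and the adhesion remark concerns infertility; the step from adhesions to more operations is an inference. Outcome 3 also covers only hysterectomy and tubal/ovarian surgery, while outcome 4 refers to any non-diagnostic surgery unrelated to pregnancy, whose rate is not a listed outcome. The point needs only that a difference is plausible.

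**Reversal.** A reader might infer that the conditional result could point the wrong way. Arithmetically it can: with damage of 6% v 5% per operated woman and the same surgery rates, events are 2.22 v 2.78, the RR among operated women is 0.83 and the RR per woman is 1.25. But that requires safer operations after non-closure. The protocol gives no reason to expect this, and adhesions would suggest harder ones. If damage per operation also rose, both ratios would point the same way, and the conditional one would only understate the harm.

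**Limited consequence.** This is one of nine M rows for closure, outcomes 2 and 3 show part of any difference in surgery, and a reader given counts by arm can do the division. Risk per operation is also a fair question about adhesions. All of this stands and keeps the point modest.

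**The SAP may settle it.** It may, and it is not shown. But the protocol itself fixes a denominator rule and words it so that outcome 4 falls outside it.

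**Conclusion.** The point holds as a should-fix matter of analysis choice. As worded, outcome 4 is compared within a group formed after randomisation whose size closure may plausibly change, and the plan's own remedy is limited to outcomes of a later viable pregnancy. The comparison is not protected by randomisation and can mask a difference in harm per woman: under the illustrative rates, RR 1.00 among operated women against 1.50 per woman.

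Every surgery and damage rate used is an assumption; only the 3,700 women per arm comes from the protocol. The figures show what can happen and do not forecast it. The documents do not support three stronger readings: that the plan expects surgery to differ by arm, that a reversal is likely, or that either denominator would detect a difference reliably.

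**What to change.** In Analysis populations, extend the two-denominator rule to outcome 4:

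- Report women with such damage over all women with follow-up data in the pair, by allocated arm, as the randomised comparison.
- Show beside it the figure among operated women, labelled as supportive, and the rate of the surgery that outcome 4 refers to (non-diagnostic, unrelated to pregnancy) by arm.

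The cost is one sentence and one extra table column. No new data are needed. The change does not add power, since events will be few with either denominator.
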